## Background

Postoperative atrial fibrillation (POAF) is a common complication following cardiac surgery with an incidence of 30–40% [1, 2]. POAF has been associated with stroke, systemic embolism, and cardiac failure. Its detection mandates additional treatment with varying combinations of drugs to control cardiac rate and/or rhythm, anticoagulation, and/or electrical cardioversion; each of which have side effects that cannot be ignored. As a result, POAF prolongs hospital stay and increases hospital expenditure [1]. Several strategies aimed at reducing the incidence of POAF have been investigated, including treatment with beta-blockers, amiodarone, and statins, all with unsatisfactory results [1, 3–5]. In a few studies, performing a posterior left pericardiotomy has been associated with a reduction in the incidence of POAF by allowing drainage of blood and fluid from the posterior pericardial space [6–8]. Performing a posterior left pericardiotomy is theorized to prevent POAF by allowing the posterior pericardial space to drain into the left side of the chest and be evacuated by a chest tube. This prevents blood and fluid from accumulating behind the left atrium, causing atrial irritation which can lead to POAF. However, previous studies are associated with some limitations such as: sample size, inclusion/exclusion criteria, randomization procedure, and suboptimal electrocardiographic monitoring strategies. Moreover, posterior left pericardiotomy requires additional operative time and can be associated with procedure-specific complications such as an increased incidence of left-sided pleural effusion. As a result, current evidence on posterior pericardiotomy has failed to translate into changes to clinical practice.

The primary objective of the present prospective, randomized, controlled study is to assess whether performing a posterior left pericardiotomy during open cardiac surgery procedures (coronary artery bypass grafting (CABG), aortic valve replacement, interventions to the ascending aorta or their combination) results in a reduction in the incidence of POAF.

The secondary objectives of this study are to assess:The time spent in atrial fibrillationThe duration of the hospitalizationSafety measures such as: pericardial and left-sided pleural effusion as a complication of this procedure, death, and major adverse events (MAE)

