#### Eligibility criteria

Included subjects will be patients undergoing open cardiac surgery for interventions on the coronary arteries, the aortic valve, and/or the ascending aorta who have no previous history of atrial fibrillation. Exclusion criteria are as follows: pre-operative non-sinus rhythm, history of previous atrial arrhythmia of any type, reoperation, mitral or tricuspid valve disease, surgery of the descending thoracic or thoraco-abdominal aorta, need for hypothermic circulatory arrest, off-pump operations, urgent or emergent presentation, disease of the left-sided pleura or previous left-sided instrumentation, non-cardiac-related comorbid contraindications to surgery, and chest deformity of any kind.

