### Methods: assignment of interventions

#### Allocation

Allocation to treatment groups will be done in a controlled, randomized fashion. In order to assure an equal distribution of cases at different risk of POAF in the two groups after enrollment, the CHADS2 score, which has been shown to predict POAF in cardiac surgery patients, will be calculated [11]. Patients will be assigned to a lower risk (CHADS2Vasc score ≤ 2) or higher risk (CHADS2Vasc score ≥ 3). The cases will, therefore, be stratified based on the CHADS2Vasc score. Subsequently, a computer-generated, mixed block randomization will be performed in order to determine assignment between the control group and the intervention group. Randomly selected block sizes of 4, 6, and 8 will ensure stratification of risk levels in each treatment. At the time of pre-surgery time-out, the circulating nurse will open a sealed envelope and reveal the group to which the patient has been assigned.

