##### Additional analyses

The primary outcomes will be tested according to the intention-to-treat principle (ITT) where all participants will be included in their assigned treatment groups regardless of the actual procedure performed. Modified intention-to-treat analysis will also be conducted. Per-protocol or as-treated analysis will also be reported as descriptive. The primary outcome analysis will be assessed by logistic regression. Baseline covariates will be included in the regression model for sensitivity analysis. These covariates include: age, sex, diabetes status, ejection fraction, extent of coronary disease, on or off pump procedure, surgical priority, and completeness of revascularization. Secondary outcomes will be analyzed for safety by descriptive statistics.

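### Three of the eight covariates in the sensitivity model conflict with the trial's own design: two are constant by eligibility, and one is set after allocation and undefined for non-coronary patients

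*Protocol article*

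**What the plan says.** Additional analyses assigns the primary outcome to logistic regression by intention to treat and then states: "Baseline covariates will be included in the regression model for sensitivity analysis". Eight covariates follow. Five describe the patient before surgery: age, sex, diabetes, ejection fraction and how extensive the coronary disease is. The other three are "on or off pump procedure, surgical priority, and completeness of revascularization".

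Three other sections bear on these last three:

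- **Eligibility criteria** lists among the exclusions "off-pump operations, urgent or emergent presentation".
- **Eligibility criteria** also defines the population as "patients undergoing open cardiac surgery for interventions on the coronary arteries, the aortic valve, and/or the ascending aorta". A patient may therefore enter without any coronary procedure.
- **Allocation** fixes when the arm becomes known: "At the time of pre-surgery time-out, the circulating nurse will open a sealed envelope and reveal the group".

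Analysis population and missing data expects missing values to be rare and provides multiple imputation for them. It names no other route.

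**The concern.** A covariate-adjusted sensitivity analysis should show that the primary result does not depend on chance imbalance in prognostic factors. For that, each covariate has to vary between patients, be fixed before allocation and exist for everyone. Pump use and surgical priority fail the first condition. Completeness of revascularization fails the second and third.

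The list cannot be used as it stands without unplanned decisions about which terms to drop and what to do with patients who had no grafts. If those decisions are made after the data are seen, the analysis loses part of its value as a check. A covariate settled in the operating room, by a team that knows the arm, can also carry part of the treatment's effect or of the surgeon's response to it.

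**Working it through.** **1. Pump use and surgical priority**

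If off-pump, urgent and emergent cases are all excluded, every eligible patient is on-pump and elective. With intercept b0 and constant columns P = 1 and S = 1, the linear predictor contains b0 + b1·1 + b2·1, and only the sum can be estimated.

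This was checked on one simulated data set of 350 patients with POAF rates of 30% vs 15%. The columns were intercept, treatment, age and the two constants.

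- The design matrix has 5 columns and rank 3.
- Maximum-likelihood logit on all five columns stops because the matrix is singular.
- A pseudo-inverse fit of the same matrix gives a treatment log odds ratio of −0.670 (SE 0.258).
- The fit with the two constants removed gives −0.670 (SE 0.258). Its intercept, −0.853, is three times the −0.284 that the pseudo-inverse fit gives to the intercept.

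The constants are therefore redundant and leave the treatment estimate unchanged.

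Some variation could remain if ineligible or converted patients stay in under intention to treat. As a rough upper guide, the Sample size section allows 5% protocol violation: 350 × 0.05 = 17.5 patients. Suppose all were off-pump or urgent, with the average POAF rate (30% + 15%)/2 = 22.5%. The coefficients would then rest on 17.5 × 0.225 ≈ 4 events.

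**2. Timing of completeness of revascularization**

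The order of events in the article is: envelope opened at the time-out, then operation, then a judgement on how complete the revascularization was. Under Blinding, only the patient is masked. The variable is therefore post-allocation.

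The possible effect of adjusting for it was simulated with 400,000 patients per scenario. All parameters were assumed:

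- conditional treatment odds ratio 0.41;
- incomplete revascularization multiplies the odds of POAF by 1.5;
- an unmeasured factor has odds ratio 2 on POAF and 0.5 on completeness.

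| Completeness, control → treated | OR unadjusted | OR adjusted |
|---|---|---|
| 84% → 85% (no effect; simulation noise) | 0.42 | 0.42 |
| 84% → 80% | 0.43 | 0.42 |
| 84% → 71% | 0.44 | 0.41 |

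The shift is small unless the procedure changes completeness a great deal.

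**3. Patients with no coronary procedure**

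These patients have nothing to grade. Multiple imputation would supply a value that cannot exist. Complete-case fitting would remove them.

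The article does not give their share, so the following range is an assumption. The power formula was first checked against the article's own 322 (30% vs 15%, 90% power, taken as two-sided 0.05, pooled variance under the null):

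n per arm = [1.960·√(2 × 0.225 × 0.775) + 1.282·√(0.3 × 0.7 + 0.15 × 0.85)]² / 0.15² = (1.157 + 0.745)² / 0.0225 ≈ 160.8, rounded up to 161. The total is 322, as stated.

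The power of a simple two-group comparison follows as Φ[(0.15·√n − 1.157)/0.581]:

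| Assumed non-coronary share | Patients left of 350 | Power |
|---|---|---|
| 0% | 350 | 92% |
| 20% | 280 | 86% |
| 40% | 210 | 74% |
| 60% | 140 | 57% |

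The table describes only a complete-case sensitivity model. It does not describe the trial's primary analysis.

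**The case against.** The case for leaving the list alone has several parts.

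- **A reader might infer that the model cannot be fitted at all.** That goes too far. An unreduced maximum-likelihood fit fails, but software that drops redundant terms returns the same treatment estimate. The constant terms are a specification error and do not cause bias.
- **A reader might infer that the adjusted effect is biased.** The article does not show this. Nothing in it says that pericardiotomy alters grafting. The Harms section lets the surgeon forgo the procedure because of extra cardiac surgery or long ischemic time, which suggests that this decision follows the main repair. Against that, the surgeon is not masked and the procedure is expected to add 15 minutes. Influence is possible, and its size is unknown.
- **A reader might infer a definite loss of patients.** That needs an unstated case mix and complete-case deletion, whereas the article names multiple imputation. A not-applicable category would keep everyone in. It would solve the missing value but not the post-allocation timing.
- **A reader might count the absence of operation type as an error.** The list is introduced in words that do not claim to be exhaustive, and further covariates may sit in the full protocol or SAP. This is a preference.

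The contradiction itself survives all of these. Three named covariates do not match the eligibility criteria or the allocation timing in the same article.

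**Conclusion.** The point holds as an inconsistency in a pre-specified sensitivity analysis, with minor to moderate severity. Three of eight listed covariates are unsuitable. Two are constant among eligible patients and can vary only through a handful of ineligible or converted cases. The third is mislabelled as baseline and is undefined for an unstated fraction of eligible patients.

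The firmest harm is the undefined value, because the only stated missing-data method does not suit it. Bias from adjusting for completeness is a risk without a demonstrated size. The simulated shifts, at most from 0.44 to 0.41, rest entirely on assumed parameters. The power figures rest on an assumed case mix and on a route that the article does not plan.

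It would be wrong to conclude that the trial's main result is undermined. The list is tied to the sensitivity analysis, so the primary intention-to-treat comparison is unaffected, and the sample size does not depend on it.

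**What to change.** In Additional analyses, delete pump use, surgical priority and completeness of revascularization from the covariate list. Keep age, sex, diabetes, ejection fraction and extent of coronary disease, with the last coded as none where there is no coronary disease. Add the CHADS2Vasc stratum used in the randomization. Every term is then known before allocation and defined for every patient.

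Planned operation type (coronary, aortic valve, ascending aorta or combined) is an optional pre-operative addition. Pump use, priority and completeness of revascularization can still be reported descriptively by arm.

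The cost is one amended sentence, made before the outcome data are examined. It needs no extra patients, since the retained and added variables are pre-operative and the stratum is already calculated for randomization.

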##### Analysis population and missing data

Authors do not expect missing data since data collection is during a short period for each patient and only one follow-up visit. In rare instances of missing data, multiple imputation analysis will be utilized. The loss to follow-up will also be reported and compared between the groups using absolute risk differences.

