#### Participant timeline

The main outcome of interest is the occurrence of POAF after cardiac surgery. Patients will first be screened for eligibility and willingness to participate in the trial. Then, informed consent will be collected from participating patients, who will be randomized into one of the two study groups. Postoperatively, patients will be closely monitored for the occurrence of atrial fibrillation, pleural and pericardial effusions. Times of event and to discharge will also be assessed. These outcomes will be monitored until the time of the follow-up visit, which will be within 30 days postoperatively for the majority of patients at our institution. Participation until this time point represents complete participation in the trial. We intend to include only patients who have completed follow-up (Fig. 2).

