#### Sample size

Two groups are necessary for this trial: the control group and the intervention group. Based on analysis performed on our aortic surgery database for the years 2012 and 2013, the incidence of POAF in cardiac surgery patients was calculated to be 37.6%. A thorough study of the academic literature, including a meta-analysis of similar studies [10] shows that intervention reduces atrial fibrillation incidence by 50%. Therefore, an atrial fibrillation incidence of 40% in the control group with a proposed decrease of 50% with intervention requires a total of 158 subjects at 80% power and 0.05 alpha. Should the incidence of atrial fibrillation be 30% in the control with a hypothesized 50% decrease, a total of 322 subjects would be required at 90% power. In order to remain conservative, account for 5% protocol violation and 10% loss to follow-up/dropout, and retain power, a total sample size of 350 (175 patients in each treatment group) will be sufficient for this study. Should the incidence of POAF be lower than expected at interim analysis, sample size calculations will be re-estimated to ensure sufficient power at the time of analysis.

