#### Retention

Before enrollment and prior to discharge, patients will be reminded and encouraged to comply with follow-up. Patients who deviate from follow-up will be contacted by phone and encouraged to complete follow-up.

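### The trial is sized for 10% loss to follow-up but has no single rule for a patient who misses the only visit, which leaves post-discharge safety outcomes exposed

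*Protocol article*

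**What the plan says.** All references are to the protocol article.

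- **Sample size.** One scenario "requires a total of 158 subjects at 80% power and 0.05 alpha"; in the other, "a total of 322 subjects would be required at 90% power". To "account for 5% protocol violation and 10% loss to follow-up/dropout" and keep power, "a total sample size of 350 (175 patients in each treatment group) will be sufficient for this study".
- **Analysis population and missing data.** This section opens by stating: "Authors do not expect missing data since data collection is during a short period for each patient and only one follow-up visit". For gaps that do arise it adds: "In rare instances of missing data, multiple imputation analysis will be utilized". Loss to follow-up is to be reported and compared between arms as absolute risk differences.
- **Retention.** "Patients who deviate from follow-up will be contacted by phone and encouraged to complete follow-up". The section mentions no recording of outcomes at that call.
- **Participant timeline.** After naming atrial fibrillation, effusions, and times to event and discharge, it says "These outcomes will be monitored until the time of the follow-up visit". It closes by stating an intention to count only patients whose follow-up is complete.
- **Additional analyses.** The primary outcome is tested by intention-to-treat, with everyone kept in the assigned arm. Secondary outcomes are analysed for safety descriptively.
- **Outcomes and Concomitant care.** POAF is defined within the hospital stay. The safety outcomes are left pleural effusion, pericardial effusion, MAE and death. Chest radiographs are daily in hospital. Echocardiography is done before discharge and again at the visit. A clinic radiograph is specified only for patients who leave with a moderate or larger pleural effusion.
- **Harms.** Serious adverse events go to the DMC, the Institutional Review Board and the principal investigator.

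**The concern.** The sections give different answers for a patient who does not return. One sizes the trial for such patients, one expects none with missing data, one would leave them out, and one keeps every randomised patient for the primary outcome. The reason given for expecting no missing data, a single follow-up visit, also works the other way: when there is only one visit, no later one can recover what a missed visit loses.

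At stake is the post-discharge part of the safety comparison, which is what any reduction in POAF will be weighed against. A patient who has died cannot attend, and one who has been readmitted may not. Absence may therefore depend on the outcome itself. Both handling rules in the article, imputing from those who came and excluding those who did not, then give rates close to the attenders' rate.

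**Working it through.** **1. The plan's own figures** (two-sided alpha 0.05, 1:1; sidedness is not stated, but two-sided reproduces both).

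- 40% v 20%, 80% power, unpooled variance: n per arm = (1.960 + 0.842)² × (0.40×0.60 + 0.20×0.80) / 0.20² = 78.5, so 79 per arm and 158 in total. Matches.
- 30% v 15%, 90% power, pooled variance under the null: n per arm = [1.960×√(2×0.225×0.775) + 1.282×√(0.30×0.70 + 0.15×0.85)]² / 0.15² = 160.8, so 161 per arm and 322 in total. Matches.

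**2. The loss planned for.** 0.10 × 350 = 35 patients, or 17.5 per arm. That is one in ten, which is hard to call rare.

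**3. What each section does with a patient who misses the visit.**

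| Section | Consequence |
|---|---|
| Sample size | expected among up to 10% |
| Analysis population and missing data | not expected; imputed if it happens; loss reported by arm |
| Participant timeline | not counted |
| Additional analyses | kept, for the primary outcome |
| Retention | phoned and urged to attend |

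The second, third and fourth rows cannot all be followed.

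**4. Which outcomes are exposed.**

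- Under the definition in Outcomes, POAF is complete at discharge. The abstract also speaks of assessing atrial fibrillation at the clinic visit, but the definition is in-hospital.
- In-hospital radiographs, the pre-discharge echocardiogram, and in-hospital MAE and deaths are also collected before the visit.
- What remains is post-discharge death, MAE and late effusion.

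**5. Size of the bias.** Let attenders have event rate e and non-attenders r × e. The ratio r is an assumption; the documents give none.

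- True rate = 0.9e + 0.1re = e(0.9 + 0.1r).
- Share of events in non-attenders, so unobserved = 0.1r / (0.9 + 0.1r).
- Excluding non-completers, or imputing them at the attender rate, reports e. Shortfall = 0.1(r − 1) / (0.9 + 0.1r).

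| r (assumed) | Unobserved share | Shortfall after either rule |
|---|---|---|
| 1 | 0.1/1.0 = 10% | 0% |
| 2 | 0.2/1.1 = 18% | 0.1/1.1 = 9% |
| 3 | 0.3/1.2 = 25% | 0.2/1.2 = 17% |
| 5 | 0.5/1.4 = 36% | 0.4/1.4 = 29% |

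If r and the loss are equal in both arms, the absolute risk difference shrinks by the same share and the relative risk is unchanged. If they differ by arm, the comparison itself is biased. If r is below 1, harm is overstated.

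**6. Bounds without r.** With 10% missing and a rate p in attenders, the true rate lies between 0.9p and 0.9p + 0.1. For an assumed p of 5% that is 4.5% to 14.5%; for 10%, 9% to 19%.

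**7. Primary outcome if the completers-only statement were applied.** Power for 30% v 15% is 92.3% with 350 patients, 89.4% with 315 (10% lost) and 87.6% with 297.5 (15% lost). For 40% v 20% it stays above 96%. The power cost is small. The larger objection is that patients would be dropped after randomisation.

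**The case against.** **The 10% may be a margin, not a forecast.** The section presents it as conservative and joins loss with dropout. That is fair: 35 is the loss the trial is built to absorb, not a prediction of 35 reachable non-attenders. A missing-data rule should still work at that level.

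**This is a condensed article.** What callers record, and whether charts are checked, may be in forms or a full protocol not shown. A reader might infer that non-attenders are phoned solely to urge attendance and that this follows from expecting no missing data. The article does not support that. It describes the call's purpose in one line, excludes nothing else, and no section links the two. The conflict between the stated rules does not depend on that inference.

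**No section says that death or MAE will be imputed.** A reader might infer this from the general imputation sentence. That sentence names no outcome, safety outcomes are to be analysed descriptively, and the completers-only statement would exclude rather than impute. This stands.

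**Death and MAE are not shown to rest on the visit alone.** They are not in the list that the Participant timeline monitors to the visit, and Harms gives a separate route for serious adverse events. This stands too, although that route describes no way of learning of an event in a patient who does not come back.

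**The magnitude rests on r.** It does, and imputation with good predictors could do better than the attender rate. The figures are illustrations.

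**Loss will be reported and compared by arm.** This would reveal an imbalance in attendance but would not recover the missing events.

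**Conclusion.** The point stands as an inconsistency with a limited but real consequence. The article plans for up to about 35 patients lost and gives no single rule for them: imputing, excluding and keeping all randomised patients are each stated somewhere. The primary result is largely protected because POAF is an in-hospital outcome, unless the completers-only statement is applied, which would contradict intention-to-treat.

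Post-discharge death, MAE and late effusion are exposed. If non-attenders have more events than attenders, either handling rule understates harm, by 9% to 29% of events for rate ratios from 2 to 5. Those ratios, a full 10% loss, and imputation at the attender rate are assumptions.

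The stronger conclusion, that late safety outcomes will be imputed instead of collected, goes beyond the text. This should be corrected, but it does not put the primary comparison in doubt.

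**What to change.** 1. **Retention.** At the call already planned, and by a check of the hospital record, record vital status, readmission, MAE and any drainage of pleural or pericardial effusion for every non-attender. Analyse these as observed outcomes.
2. **Analysis population and missing data.** Limit multiple imputation to imaging findings that cannot be obtained. Replace the expectation of no missing data with the 10% allowed in Sample size. This wording change alone would alter no result; the data collection in item 1 is what reduces the bias.
3. **Participant timeline.** Remove the completers-only statement, so that all randomised patients are analysed as Additional analyses requires.

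The cost is a few questions and a record check for about 35 patients, plus protocol wording. The downside is that phone and record data are less detailed than a visit and will not replace the follow-up echocardiogram.
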